### 4.1. Limitations

A methodological limitation that is worth highlighting is the size of the sample, which is limited by the official ratio of students per internship group and could reduce the statistical power of the study, making it difficult to detect significant small differences between subgroups. To mitigate this issue, the use of non-parametric tests will be prioritized. In addition, the study is planned as a pilot, whose main objective is to validate the statistical trend and effect size for future multicenter trials.

Regarding the randomization of entire natural groups rather than individuals, there is a risk that the groups may not be entirely homogeneous at baseline. Specifically, having only one cluster per arm constitutes a major design limitation, as the intervention effect may be confounded with cluster-level differences. Therefore, any efficacy comparisons between groups in this pilot phase are strictly exploratory. To address this, a strict statistical verification of comparability will be conducted. If significant baseline differences are detected, they will be explicitly reported and considered potential confounding variables during the interpretation of results, acknowledging that parametric adjustment methods may not be applicable given the sample size constraints.

It is important to acknowledge that the assessment of academic performance acquisition in this study is restricted to the cognitive domain (knowledge and theoretical decision-making), which will be measured via written tests. Due to the pilot nature of the study and logistical constraints, objective measures of psychomotor clinical competence or behavioral transfer to practice, such as Objective Structured Clinical Examinations or checklists in high-fidelity environments, will not be included. Future phases of this project will aim to incorporate these practical dimensions to evaluate the ‘transfer of training’ to the bedside.

It should be noted that there may be a “Novelty Effect” and the improvement in initial performance may simply be due to the novelty of using technology (Wix) in class and not to the specific narrative adaptation. The longitudinal design of four sessions (spanning four consecutive weeks) will help to dilute this effect. By monitoring the students over a one-month period, which corresponds to the ‘first few weeks’ where initial motivation typically decreases, we can determine if engagement is maintained until the final session.

As the researcher is also the teacher who evaluates the coursework, this could introduce unconscious bias (Pygmalion Effect) to favor the EG or generate in the students a desire to please the teacher by responding positively to the surveys. To address this situation, the knowledge-assessing questionnaires contain multiple-choice questions to facilitate automatic and objective correction and eliminate subjectivity on behalf of the evaluator. Anonymity will be guaranteed for the satisfaction surveys to encourage honesty.

As for the profile self-evaluation through the PPDS, the classification of the students depends on their sincerity when answering the test. It may be that a “Toxic” student does not recognize themselves as such and marks “Coacher” answers due to social desirability, thus being assigned a narrative that does not correspond accurately to their profile. This issue will be addressed by clearly explaining that there are no “good or bad” profiles, thus reducing social pressure.

Another limiting aspect is the risk of contamination between groups. As students are classmates from the same faculty, the CG students may learn about the existence of the EG’s “special missions” and feel demotivated (demoralizing effect) or try to obtain the EG passwords. To address this issue, Wix login passwords will be changed on a per-session and group basis, and explicit confidentiality will be required as part of the “game contract”. To actively monitor this risk without increasing survey fatigue, the Principal Investigator will utilize the pre-established “field diary” to record any spontaneous student disclosures or observable evidence of cross-contamination between the shifts. Any detected contamination will be reported as a feasibility metric and factored into the interpretation of the exploratory efficacy results. While this observational approach is suitable for a pilot, future definitive trials will benefit from incorporating a formal self-report question to empirically measure cross-contamination rates.

Finally, as a logistical limitation, and given the nature of the study, failures in the faculty’s Wi-Fi connection, Wix server crashes, or problems with students’ mobile devices could interrupt the intervention. An alternative plan will be available, with changes in the teaching schedule agreed upon with the students so that a new practical session may be scheduled.

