## Abstract

**Background/Objectives**: Simulation-based education often lacks personalization, focusing on technical competence rather than individual student profiles. This protocol describes a study designed to evaluate whether adapting gamified narratives to nursing students’ personality profiles has the potential to support academic performance in obstetrics. This study aims to validate the integration of psychometric profiling and AI as a sustainable strategy for personalized clinical training. **Methods**: A cluster-randomized controlled longitudinal pilot trial will be conducted at the University of Atlántico Medio. The protocol has been submitted for registration at ClinicalTrials.gov (Registration Pending). Thirty-eight second-year nursing students meeting inclusion criteria (excluding repeaters or those with prior specialized training) will be assigned by natural practice to either a control group (generic gamification) or an experimental group (gamification adapted according to Player Personality and Dynamics Scale profiles using AI-generated content). The intervention comprises four clinical simulation sessions focusing on pregnancy and childbirth, which are managed via the Wix platform. The primary outcome is academic performance, measured as “Learning Gain” (post-test scores minus pre-test scores). Secondary outcomes include student satisfaction measured via the Gameful Experience Scale. Data will be analyzed using Mann–Whitney U tests to compare overall efficacy and intragroup evolution. To minimize observer bias, knowledge assessments will utilize automated, objective scoring, and participants will be blinded to the study hypothesis. **Expected Outcomes**: The study aims to establish the technical and pedagogical feasibility of integrating AI-adapted narratives into nursing curricula. It is anticipated that the personalized approach will show positive trends in learning gains and engagement patterns, providing a baseline for larger multicenter trials. **Conclusions**: This protocol presents a framework for “Precision Education” in nursing, shifting from “one-size-fits-all” simulations to student-centered adaptive training. The use of Generative AI makes such personalization sustainable and cost-effective for health science faculties.

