Despite the increasing adoption and demonstrated value of simulation and gamification in nursing and midwifery [11,12], there is marked heterogeneity in its implementation in different studies and programs, leading to disparities in assessment designs and tools [2,13,14]. In the context of simulation-based education, the lack of global consensus on how to assess or integrate skills is reflected in the fact that curricula are often based on the number of cases completed rather than objective outcomes [13,15]. In addition, the efficacy of educational interventions is intrinsically linked to specific characteristics such as the content, “dose”, and optimal methodology, aspects that still require identification through experimental studies [9,16]. There is a risk of the “novelty effect”, where initial motivation may decrease after the first few weeks if the challenge is not maintained or if the content is not properly adapted [17].

The lack of a personalized approach means that training often focuses on technical competence without fully integrating interpersonal skills and factors from the clinical setting, such as communication with patients and peers [15,18]. Consequently, existing programs do not always adapt optimally to individual student needs or facilitate long-term skill retention, as most studies do not perform deferred post-intervention measurements to ensure the permanence of acquired knowledge [2].

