### 2.8. Outcome Variables

The main outcome variable will be academic performance, LG, understood to reflect new knowledge acquired on the subject under study. The degree of assimilation of the theoretical and practical concepts of pregnancy and childbirth in each of the four clinical cases will be evaluated. To this aim, an “ad hoc” questionnaire comprising 40 multiple-choice questions was designed by the PI, who is a certified Nurse Specialist in Obstetrics and Gynecology (Midwife) and the lecturer in charge of the class. The items were constructed to strictly align with the specific curricular contents and learning objectives of the ‘Reproductive Health’ syllabus. To ensure external content validity prior to administration, this initial draft will be reviewed by an external panel of five experts (three academic midwives and two obstetricians). Regarding reliability, since this is a pilot study, internal consistency and item analysis will be calculated post hoc to validate the instrument for future trials. The questions in the final questionnaires (administered post-simulation at each session) will address the same content as the initial questionnaire, but the form and order of the answers will be modified. Learning gain will be calculated using a simple difference (post-test score minus pre-test score), normalizing the results on a scale of 0 to 10 points. An arithmetic mean of the learning gain scores obtained from the four use cases will be calculated.

The secondary outcome variables will be

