-Satisfaction: The students’ subjective perception of the usefulness, fun, and motivation generated by the activity will be evaluated using the Gameful Experience Scale (GAMEX) [28]. This validated 27-item instrument in Spanish is suitable for measuring game experience in nursing students’ training. It uses Likert-type responses to measure the multidimensional nature of the gamified experience in the educational context. The six dimensions include enjoyment, abstraction, creative thinking, activation, absence of negative effects, and mastery. This model demonstrated high overall reliability, with a Cronbach’s alpha of 0.85. The scoring format uses a five-point Likert scale. In the proposed study, measurement will be conducted exclusively at the end of the intervention (Session 4) to capture the students’ overall perception of the program. Prior to analysis, items with negative wording (reverse punctuation) will be recoded so that higher scores consistently reflect a more positive experience. The statistical report will present results for both the total aggregate score and the independent mean scores for each of the six dimensions.-Player Profile: the students’ psychological and behavioral predisposition to game dynamics and narratives will be assessed using the PPDS in its validated Spanish version [21]. The PPDS is a psychometrically validated instrument composed of 21 items rated on a six-point Likert scale specifically designed to identify player profiles in the context of educational gamification based on narratives to measure the frequency of certain behaviors, where 1 means “Never” and 6 means “Always”. After a student completes the questionnaire, the system does not place them in a single category but generates five independent scores, one for each profile, showing which of the following profiles they align with the most: Tryhard (achievement- and competency-oriented); Coacher (oriented toward leadership and help); Esthetic (narrative and visual beauty-oriented); Joker (oriented to humor and surprise); or Toxic (a technical gamification term referring to players oriented toward testing system limits, seeking loopholes, or disrupting boundaries, often associated with lateral thinking rather than a negative personal judgment). The scale demonstrated high overall reliability (omega = 0.93).-Gamification Experience: Previous experience in gamification will be evaluated using the following question: Have you participated in similar activities before? The students can respond “yes” or “no”.-Sociodemographic variables: Age is understood as the time that a person has lived, counting from birth to the time of the survey, measured in whole years; gender is understood as a variable that refers to the social and cultural construction that defines the roles, behaviors, activities, and attributes that a society considers appropriate, with the answer options male, female, and non-binary; and the average grade considered to mean the average grade achieved in the first year of the nursing program to monitor the differences between the groups.-Feasibility and implementation outcomes: given the pilot nature of this trial, the following feasibility metrics will be formally tracked to inform the design of the subsequent definitive trial: recruitment rate, retention rate, technical failure rate, time-on-task compliance, and qualitative evidence of cross-contamination.

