A descriptive analysis of sociodemographic data and previous experience will be carried out, qualitative variables will be presented as absolute and relative frequencies, and quantitative variables will be presented as medians and interquartile ranges (if the distribution is not normal) or means and standard deviations if the distribution is normal.

To compare the overall efficacy (CG versus EG), the homogeneity at baseline will be checked. The Pre-test (Form 0) scores and the average grades according to academic records will be compared between both groups using the Mann–Whitney U test to ensure that the groups are comparable despite the cluster randomization. Additionally, prior gamification exposure and the distribution of PPDS profiles will be descriptively compared at baseline to identify any major initial imbalances between the clusters

To test the primary hypothesis, the mean global LG of the four sessions between the CG and the EG will be compared using the Mann–Whitney U test for independent samples. Given that the study design involves two natural clusters of unequal size (n = 18 and n = 20), the main hypothesis test will be performed at the participant level. Given the limitation of having only one cluster per arm, inferential statistics will be considered strictly exploratory, and results must be interpreted with caution.

Regarding the secondary outcomes, the analysis of the five PPDS profiles will be strictly descriptive and exploratory, given the limited sample size. Subdividing the experimental group (n = 20) into five profile categories yields cell sizes too small for robust inferential statistics; hence this approach prioritizes statistical rigor by avoiding underpowered hypothesis testing on these specific sub-variables.

To analyze the students’ perception at the end of the study, the satisfaction scores (GAMEX) will be compared between groups using the Mann–Whitney U test. Finally, an exploratory Spearman correlation analysis will be performed between satisfaction and LG to determine if the students who enjoyed the experience the most were also those who learned the most.

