## 3. Expected Outcomes

As a study protocol, this article does not report empirical findings. However, based on the proposed design, the study is anticipated to generate data in the following categories:-Feasibility and implementation: The primary outcome is to establish the technical and pedagogical feasibility of integrating AI-generated narratives into the standard nursing curriculum. We expect to report completion rates, time-on-task data, and technical bottlenecks identified in the Wix platform.-Academic performance trends: Regarding the LG, the study will provide preliminary estimates of the effect size comparing the adapted (EG) versus generic (CG) methodologies. Rather than confirming statistical superiority, the data will determine if the personalized approach shows a positive trend that justifies the calculation of a larger sample size for future randomized clinical trials.-Engagement patterns: Through the exploratory analysis of the PPDS profiles, we anticipate characterizing how different personality types interact with the gamified elements. We expect to describe whether specific profiles show differential satisfaction scores compared to the standard user, providing a baseline for tailored educational strategies.-Correlation data: We expect to obtain statistical evidence regarding the relationship between student satisfaction (GAMEX scores) and academic performance, clarifying whether higher engagement correlates with actual knowledge retention in this specific demographic.

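### Maintained engagement, knowledge retention and within-group evolution are promised, but the measurements and the named test do not support them as written

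*Protocol article*

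**What the plan says.** **Engagement.** Section 4.1 names a possible novelty effect and answers that, by following students for a month, "we can determine if engagement is maintained until the final session". For GAMEX, section 2.8 says "measurement will be conducted exclusively at the end of the intervention (Session 4". Section 2.10 uses GAMEX in a between-group comparison and in a correlation with learning gain (LG). The feasibility metrics in section 2.8 are "recruitment rate, retention rate, technical failure rate, time-on-task compliance, and qualitative evidence of cross-contamination".

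**Retention.** Section 3 expects the correlation between GAMEX and academic performance to help by "clarifying whether higher engagement correlates with actual knowledge retention in this specific demographic". On timing, section 2.8 has: "The questions in the final questionnaires (administered post-simulation at each session". No later knowledge test is described. The Introduction observes of the field that "most studies do not perform deferred post-intervention measurements to ensure the permanence of acquired knowledge".

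**Within-group evolution.** The Abstract states: "Data will be analyzed using Mann–Whitney U tests to compare overall efficacy and intragroup evolution". Section 2.10 says of the primary outcome that the arms "will be compared using the Mann–Whitney U test for independent samples", after averaging LG over the four sessions for each student. It gives no paired or repeated-measures analysis, and it says that no separate analysis plan exists.

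**The concern.** Each statement promises something about time: engagement lasting, knowledge persisting, a group changing. Each needs either repeated measurements that are analysed as such or a test that respects pairing. The plan supplies neither for these purposes.

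What is at stake is the results paper. The engagement sentence is offered as mitigation of an acknowledged threat, so a reader may take that threat as dealt with. A correlation with immediate gain could be reported as evidence about retention. If the Abstract were followed literally, before and after scores from the same students would be analysed as if they came from different people, in arms of only 18 and 20.

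**Working it through.** The document states no power, effect size or variance, so it has no figure to reproduce. The check sets each statement beside its measurement and its analysis.

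| Statement | Measurement | Planned analysis | Gap |
|---|---|---|---|
| Engagement maintained (4.1) | GAMEX once, after Session 4 (2.8) | Between arms; one correlation with LG (2.10) | No within-student change in GAMEX can be formed |
| Knowledge retention (3) | Post-test in the same session as the simulation (2.8) | Spearman with LG (2.10) | No measurement after a delay |
| Intragroup evolution (Abstract) | Pre and post scores per student (2.8) | Mann–Whitney U (Abstract); nothing within group (2.10) | Unsuitable test, and absent from the detailed plan |

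**Could another series carry the engagement claim?** Attendance signatures (2.7), time-on-task (2.8 and 3), the field diary (2.11) and LG by session (2.10) all exist. None is defined as engagement and none has a planned analysis over sessions. Section 3 moves from GAMEX scores to engagement as if they were the same thing. LG by session measures knowledge on four different topics and is averaged before the arms are compared. The schedule figure is not shown, but the word exclusively in section 2.8 settles the GAMEX timing.

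**What does Mann–Whitney do with paired scores?** The inputs are the arm sizes 18 and 20 and the 0.05 level from section 2.10 (taken as two-sided). The pre-post correlation ρ, the shift in SD units and normality are assumptions.

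With positive correlation, the null variance of the pre-post contrast shrinks by roughly 1 − ρ, but the test still uses the independent-samples variance. Approximately:

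type I error ≈ 2 × [1 − Φ(1.96 / √(1 − ρ))]

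At ρ = 0.5: 1.96 / √0.5 = 2.77, and 2 × [1 − Φ(2.77)] ≈ 0.0056, or about 0.6%.

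Simulation, 4,000 runs per cell, shift 0 for type I error and 0.5 SD for power:

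| n | ρ | Type I error: Mann–Whitney | Type I error: Wilcoxon | Power: Mann–Whitney | Power: Wilcoxon |
|---|---|---|---|---|---|
| 18 | 0 | 0.044 | 0.047 | 0.278 | 0.267 |
| 18 | 0.3 | 0.024 | 0.054 | 0.273 | 0.396 |
| 18 | 0.5 | 0.008 | 0.052 | 0.229 | 0.496 |
| 18 | 0.7 | 0.002 | 0.048 | 0.197 | 0.699 |
| 20 | 0 | 0.046 | 0.048 | 0.327 | 0.316 |
| 20 | 0.3 | 0.021 | 0.046 | 0.282 | 0.394 |
| 20 | 0.5 | 0.010 | 0.046 | 0.279 | 0.548 |
| 20 | 0.7 | 0.001 | 0.050 | 0.245 | 0.762 |

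For a 0.6 SD shift with n = 19 (the mean of the two arm sizes), separate simulations give power of 38% to 39% for Mann–Whitney against 67% to 69% for Wilcoxon at ρ = 0.5. At ρ = 0.7 the figures are about 37% against 88% to 89%. The two tests agree only when ρ = 0.

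**The case against.** The other side has real points, and most of them limit the scope.

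- *Session-level information is collected.* This stands. A reader might infer that no trajectory of any kind could be described; the document does not support that. The gap is that nothing collected is designated as engagement or analysed over sessions.
- *The novelty named in section 4.1 is that of using Wix in class, and both arms use Wix.* This stands. A reader might infer that novelty biases the comparison of arms. Platform novelty is shared, so it does not by itself do so; only novelty specific to the adapted elements could. Section 4.1 also makes the milder claim that four sessions dilute the effect, and averaging LG is consistent with that.
- *Retention is neither a hypothesis nor an outcome.* This stands. LG is defined as newly acquired knowledge, and section 2.10 frames the correlation in terms of learning. The word in section 3 is still wrong for what is measured.
- *The unsuitable test appears only in the Abstract, and its error is conservative.* This stands. Section 2.10 applies Mann–Whitney only between arms, so the simulated loss belongs to an analysis that the detailed plan never specifies. A reader might fear false positive findings; with positive correlation the error runs the other way.
- *Efficacy inference is already labelled exploratory.* This tempers conclusions from data that are collected. It does not supply a missing time point or make an independent-samples test suitable for paired scores.
- *A second GAMEX conflicts with the anonymity promised for satisfaction surveys in section 4.1.* This is weak, because correlating GAMEX with LG already requires linkage by student. The wording would still need reconciling.

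**Conclusion.** The point holds as a mismatch between three secondary statements and the plan that should support them. The engagement statement is the most serious, because it claims a capability: GAMEX provides no within-student contrast over time, and no substitute is designated. Retention is a wrong word for a same-session measurement. Intragroup evolution is promised in the Abstract with a test unsuited to paired data, and section 2.10 does not carry it out.

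The primary between-arm estimate and the planned GAMEX comparison are untouched. The power figures illustrate the cost of following the Abstract literally. They rest on an assumed correlation, shift and normality, none of which the document gives. Over assumed correlations of 0.3 to 0.7 and a 0.5 SD shift, Mann–Whitney type I error runs from 0.024 down to 0.001, and its power is 0.20 to 0.28 against 0.39 to 0.76 for the paired test.

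**What to change.** 1. **Engagement.** In section 2.10, define time-on-task, recorded per student and session, as the engagement series and report it by arm at each session; or delete the sentence in section 4.1. The metric is already on the tracking list, so the cost is analysis text. Because topics differ between sessions, the arm difference within each session is more informative than the raw trend. A second GAMEX after Session 1 is optional: it costs one extra 27-item form, must be linked by the student code, and must be reconciled with the anonymity promise in section 4.1.
2. **Retention.** In section 3, replace knowledge retention with immediate post-session knowledge gain. This is wording only.
3. **Within-group evolution.** State in section 2.10 that pre-post change within each arm is tested by Wilcoxon signed-rank and reported with an effect size and 95% confidence interval; or remove intragroup evolution from the Abstract. LG is already the paired difference, so no new data are needed. Do not use a Friedman test across the four sessions as evidence of evolution, because it would confound time with topic.

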Consequently, the aim of this study is to evaluate the effectiveness of a profile-adapted gamified intervention compared to a generic gamified intervention in improving the academic performance of nursing students regarding obstetric competencies upon completion of the four-week program. Based on this aim, the following hypotheses are proposed:-Primary hypothesis—the Experimental Group (EG), with exposure to the profile-adapted narrative, will demonstrate a significantly higher global Learning Gain (LG) compared to the Control Group (CG) receiving generic gamification.-Secondary hypothesis—there is a positive correlation between the level of student satisfaction and academic performance (LG) regardless of the group.

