
### 2.9. Data Collection Method

The study employs a hybrid data collection strategy to clearly separate the educational game mechanics from the research evaluation process. All formal assessments related to the study outcomes—including sociodemographic data, the PPDS, and the knowledge tests—will be administered exclusively in physical paper format. This ensures that research data collection does not depend on the stability of the digital platform during the session. Google Forms will be used solely as a functional component of the gamification (acting as “digital locks”). Participants enter their clinical answers into these forms to obtain the passwords required to advance through the Wix narrative. These digital responses serve an instructional purpose and are not the primary source for academic performance analysis.

To ensure high-quality data and minimize errors during the transition from paper to digital analysis, each student will be assigned a unique alphanumeric code on their first paper form (Form 0), which must be manually transcribed by the student onto all subsequent paper assessments (Forms 1F to 4F) to enable longitudinal matching. The PI will manually enter the data from the paper forms into a pre-configured offline database. To promote data integrity, a random 10% sample of the paper forms will be cross-checked against the digital database by a co-author to ensure transcription accuracy.

The primary strategy for participant retention is the integration of the trial into the mandatory face-to-face academic calendar. The educational value of the simulations as preparation for the final exam serves as the main incentive for completion. Reasons for any missing sessions or incomplete paper forms will be recorded in the field diary to be reported as feasibility outcomes.

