### 2.11. Data Protection and Trial Management

To ensure anonymity and facilitate longitudinal data matching, a double-layer security protocol will be applied. A third-party platform, Google Forms, will be used under the PI’s license solely as a data entry interface, while the intervention will be hosted on Wix. Crucially, user registration with personal emails will not be required on Wix; access will be facilitated using generic passwords or role codes provided by the teacher.

Each student will be assigned a unique alphanumeric code to allow for traceability without revealing personal identities in the final statistical matrix. The master database containing the link between the code and the participant’s identity will be stored locally and guarded exclusively by the PI on a device with encrypted storage and protected by double-factor authentication. This master file will be destroyed once variable cross-referencing is complete. Due to the short duration and educational context of the pilot, interim analyses are not planned.

Given that the PI also teaches the subject, the analysis of the research data will be carried out strictly after the official transcripts of the participating students have been finalized and locked. This temporal separation ensures that the students’ performance in the “game” cannot bias their official grade.

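### The satisfaction survey is promised as anonymous, but the planned analysis needs it linked to each student and the teacher holds the identity key, so the protection against pleasing the teacher is weaker than stated

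*Protocol article*

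**What the plan says.** Section 4.1 (Limitations) names the bias directly. The teacher's double role could "generate in the students a desire to please the teacher by responding positively to the surveys". For the knowledge tests it offers objective scoring. For the satisfaction survey it offers one remedy: "Anonymity will be guaranteed for the satisfaction surveys to encourage honesty".

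The secondary hypothesis in Section 1 is that "there is a positive correlation between the level of student satisfaction and academic performance (LG) regardless of the group". Section 2.10 (Data Analysis) tests it thus: "an exploratory Spearman correlation analysis will be performed between satisfaction and LG". No stratification or adjustment by arm is mentioned. GAMEX is given once, at Session 4 (Section 2.8).

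Matching across forms works through a code. Section 2.9 gives each student one on Form 0, "which must be manually transcribed by the student onto all subsequent paper assessments (Forms 1F to 4F) to enable longitudinal matching". The same section has the PI key in the paper forms by hand. Section 2.11 gives the purpose of the code: "Each student will be assigned a unique alphanumeric code to allow for traceability without revealing personal identities in the final statistical matrix". The file that ties code to identity "will be stored locally and guarded exclusively by the PI" and is destroyed once cross-referencing is finished.

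**The concern.** Anonymity is offered as protection against one particular person, the teacher. It works only if that person cannot tell who gave which answer, and if the students can believe so when they fill in the form. Under the arrangements in Sections 2.9 and 2.11, the teacher is the person who can tell.

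Two things are at stake. GAMEX scores stay open to the upward bias that the promise was meant to remove, which affects the between-group satisfaction comparison and the correlation with LG. In addition, students who depend on this teacher for their grade receive an assurance that the plan does not deliver as written.

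A smaller, separate point concerns the correlation. The hypothesis is about a relation that holds whatever the group, but a coefficient computed over all students mixes the relation within arms with any difference between arms.

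**Working it through.** **Part 1: linkage and custody.** The plan states no figure to reproduce here, so the check is to ask which planned outputs need GAMEX joined to other data on the same student.

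- GAMEX compared between groups (Section 2.10): needs only a group label.
- GAMEX correlated with LG (Sections 1 and 2.10): needs one pair per student.
- Gender differences in satisfaction (Section 2.10): needs GAMEX joined to gender.
- Satisfaction by player profile (Section 3): needs GAMEX joined to the PPDS result.

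Three of the four need an individual link, so GAMEX must carry a code. The next question is who can turn that code into a name.

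- The identity file is held by the PI alone (Section 2.11).
- The paper forms are entered by the PI (Section 2.9).
- The PI teaches the subject and evaluates the coursework (Sections 2.11 and 4.1).

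The remaining safeguards can be tested against the same question.

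- Identities are left out of the final matrix (2.11). This acts after data entry.
- The key is destroyed (2.11), but only after cross-referencing, so it exists while GAMEX is collected and entered.
- Analysis waits until transcripts are locked (2.11). This restricts analysis and says nothing about data entry or sight of the forms.
- A non-teaching co-author analyses data with masked groups (2.5). This hides the arm from the analyst. It does not hide the respondent from the PI.

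None of the four prevents the PI from identifying a respondent while handling the forms.

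**Part 2: pooling over arms.** Inputs from the protocol: 18 and 20 students (Sections 2.7 and 2.10). Assumed, because the protocol gives no values: zero correlation within each arm, and the same standardised arm difference d, in the same direction, on GAMEX and on LG, with within-arm SD equal to 1.

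With p the product of the two arm proportions, the between-arm covariance is p·d² and each pooled variance is 1 + p·d². Hence

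pooled r = p·d² / (1 + p·d²), with p = (18 × 20) / 38² = 360 / 1444 = 0.249.

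| Assumed d (SD) | p·d² | Pooled r |
|---|---|---|
| 0.5 | 0.062 | 0.062 / 1.062 = 0.06 |
| 0.8 | 0.160 | 0.160 / 1.160 = 0.14 |
| 1.0 | 0.249 | 0.249 / 1.249 = 0.20 |

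This is a Pearson formula used as an approximation to the planned Spearman coefficient. If the arms differ in opposite directions on the two variables, the sign reverses. For scale, the Fisher-z half-width of a 95% interval with 38 pairs is about 1.96 / √35 = 0.33.

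**The case against.** A reader might infer that the secondary hypothesis cannot be tested at all, since unlinked surveys would give 0 of 38 usable pairs. The documents do not support that reading. Section 2.11 introduces the code as a means to both anonymity and longitudinal matching, so the protocol itself uses the word for coded data. Given the planned correlation, the coherent reading is that GAMEX carries the code. Section 2.9 does not name GAMEX among the paper forms, and Figure 1 is not available, so how it is coded cannot be seen. The between-group comparison survives on either reading.

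A reader might also infer that students have no protection. That goes too far: the final matrix carries no identities, the key is eventually destroyed, and analysis follows the locking of transcripts and is done by someone else. These are real confidentiality measures. They do not amount to anonymity towards the teacher, which is what Section 4.1 offers.

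On pooling, it would be wrong to say that any arm difference produces a positive correlation; only differences in the same direction do. The protocol does anticipate that direction, since the Abstract expects positive trends in both learning gain and engagement. Even so, the distortion is modest beside the sampling error at this sample size. The correlation is labelled exploratory, and the hypothesis can be read as meaning all students together. This supports reporting an adjusted coefficient as a refinement. It does not make the pooled one a serious defect.

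Finally, moving the whole identity key away from the PI would collide with Section 2.7, under which the PI hands each experimental-group student a profile-specific code at every session. That objection is sound, and the fix below allows for it.

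**Conclusion.** The inconsistency stands. Section 4.1 guarantees anonymity as the remedy for answers given to please the teacher, while the planned linkage and the PI's sole custody of the key make the survey at best coded and re-identifiable by that teacher. The stated protection against social-desirability bias is therefore weaker than claimed. How much bias follows cannot be quantified from the documents.

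The conclusion rests on one inference, that GAMEX carries the study code or an equivalent. The protocol does not say so, but three planned outputs require it.

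The pooling point is separate and smaller: about 0.06 to 0.20 of spurious correlation under the assumed same-direction differences of 0.5 to 1.0 SD.

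Severity is moderate to minor. A secondary outcome and an exploratory correlation in a pilot are affected; the primary comparison of LG between arms is not.

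**What to change.** 1. In Section 4.1, replace the guarantee of anonymity with a statement that the survey is coded and not identifiable to the teacher. Tell students the same before Session 4.
2. State in Section 2.9 that GAMEX carries the study code. Have students return it in a sealed envelope to the non-teaching co-author, who enters it and joins it to LG by code.
3. Release no individual GAMEX data to the PI until transcripts are locked, and preferably not before the key has been destroyed as Section 2.11 already plans. The PI can keep the student-to-profile list needed to hand out experimental-group codes under Section 2.7.
4. In Section 2.10, report the satisfaction–LG Spearman correlation adjusted for arm (partial) or within each arm, with a 95% CI, beside the pooled value.

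The cost is one extra form per student, at most 38, for the co-author to handle and enter, plus a few lines of text and one extra coefficient. Sealed return means the co-author need not attend the session. No additional students, visits or instruments are needed.
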